## 9.2 Assessments of outcomes

### 9.2.1 Assessment of primary outcome

Primary outcomes measures will be

- a) the number of Heavy drinking days (HDD, i.e. the number of days with 6 standard drinks or more, equivalent to 60 grams of pure alcohol or more) over the last month, and
  - b) the Short Inventory of Problems (SIP) total score (Kiluk *et al.*, 2013),
- both measured over 3 follow-up times (3-, 6-, and 12-month after intervention).

HDD will be measured using a 30-day Timeline Follow-back technique (TLFB; Sobell and Sobell, 1995). This technique will be used by a trained interviewer and consists in asking participants to retrospectively estimate their daily alcohol consumption over a time period (i.e., 30 days in the current study) prior to the interview. To help participants provide retrospective estimates of their daily alcohol use, the interviewer uses a calendar with temporal anchors such as holidays, week-end days, local festivals or parties, participant's activities, etc.

The SIP is a validated 15-item scale to evaluate alcohol-related problems.

### 9.2.2 Assessment of secondary outcomes

Secondary outcomes measures will be

- a) Weekly drinking amount (i.e. number of drinks per week, derived from the TLFB).
- b) Frequency of alcohol-related consequences (derived from 4 alcohol-related consequences adapted from Wechsler *et al.*, 1994). Consequences will be measured over the same 3 follow-up times (3-, 6-, and 12-month after intervention).
- c) SIP sub-dimension scores (Physical, Social, Intra-personal, Inter-personal, and Impulse control; Kiluk *et al.*, 2013). These scores will be measured over the same 3 follow-up times (3-, 6-, and 12-month after intervention).
- d) Proportion of patients with hazardous or harmful drinking status (Alcohol use disorder identification test - AUDIT score  $\geq 8$ ; Babor *et al.*, 2001) at 12-month follow-up. The reference period is 12 months and will thus be assessed only at this follow-up.
- e) Proportion of patients who started alcohol treatment and of patients readmitted to the ER over the 12-month follow-up period. These will be measured by asking the participant at 3 follow-up times (3-, 6-, and 12-month after intervention).
- f) Proportion of patients who started alcohol treatment and of patients readmitted to the ER according to Lausanne University Hospital medical records. Participants' records over the 12 months following inclusion visit will be consulted by a research assistant at the end of the data collection process.
- g) Heavy drinking according to Ethyl glucuronide (EtG) concentration in head hair. EtG has been presented as the only biomarker that can conclusively discriminate active heavy drinkers from social and non-drinkers (Crunelle *et al.*, 2014). Participants in the present study will be asked for consent to take a 2-3 centimeters long strand of hair (diameter of pencil lead) for EtG testing at baseline, 6-, and 12-month follow-up. Laboratory testing of EtG will be conducted at the end of the data collection process.

### **9.2.3 Assessment of other outcomes of interest**

Other variables of interest will be variables for mechanisms of change analysis (see Chapter 5.3 for a list). These variables will be assessed by trained research clinicians/assistants using validated scales.

### **9.2.4 Assessment of safety outcomes**

Not applicable.

### **9.2.5 Assessments in participants who prematurely stop the study**

Participants withdrawing from the trial will not be contacted for subsequent questionnaires. However, if they consented to within the initial consent process, their hospital administrative records will be consulted (readmission in the ER and alcohol treatment) at 12 months post baseline.

## **9.3 Procedures at each visit**

### **9.3.1 Day 1 – Inclusion, Baseline procedures, Intervention (in the ER)**

- A. Inclusion/Exclusion criteria from medical file/ER exam
  - Age
  - Blood alcohol concentration at admission (test made by ER staff)
  - Life threatening conditions
  - Detainees or medico-legal admissions
  - Medical or psychiatric contraindications preventing contact with patient
- B. Inclusion/Exclusion criteria assessed by research staff
  - Being fluent in French
  - Not currently receiving another alcohol or substance use treatment
- C. Consent process
  - Information sheet
  - No psychiatric or medical contra-indications preventing patients understanding informed consent, fulfilling questionnaires, and participating in the intervention (evaluated using an adaptation of the University of California, San Diego Brief Assessment of Capacity to Consent; McCormack et al. 2014)
  - Signing consent form
- D. Contact information
  - Name, Address, Phone
- E. Baseline questionnaire
  - Socio-demographic questions
  - Alcohol Use Disorder Identification Test
  - Substance use
  - Attribution of ER admission to alcohol
  - Readiness Rulers
  - Alcohol-related expectancies
  - Actual-ideal drinking discrepancy
  - Depression
  - Quality of Life
- F. Randomization
  - Software-based automatic allocation to study group (BMI vs BA)
- G. Intervention
- H. Post-session questionnaire
  - Patient rating of the treatment (paper/pencil questionnaire to be placed in a sealed envelope by the participant and later entered by research assistant to avoid that research

- clinicians have access to participant's rating of the session)
  - Readiness Rulers
  - Actual-ideal drinking discrepancy
- I. Counselor's rating of the treatment
  - Working alliance inventory
- J. Head hair sampling for Ethyl Glucuronide concentration analysis
  - Additional information and consent procedure
  - Sampling of 2-3 centimeters long strand of hair (diameter of pencil lead)
- K. Additional information on admission (medical records, not in presence of patient)
  - Admission and discharge time
  - Diagnosis
  - Use of restraints
  - Passage in resuscitation area
  - Orientation at ER discharge

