#### **1.7.4.2 Interventionists**

Two or three interventionists will be hired over the study. They will conduct both types of interventions. They will also conduct patients' recruitment and inclusion, baseline assessment, and collect post-session patient's questionnaires.

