The participants will be ask if they consent to participate in the questionnaires (baseline and follow-up) and the intervention which are the essential parts of the study. Additional (optional consent) will be asked for the audio-recording of the intervention and consultation of their hospital administrative and medical records. Participants refusing these optional consents will not be excluded from the study.

The participant will date and sign the informed consent form. Then the form will be dated and signed by the research clinician. A copy of the fully signed informed consent will be given to the participant together with the information sheet. The originally signed informed consent will be retained as part of the study records.

An additional consent procedure will be conducted at the end of the baseline procedures. Participants will be asked for consent to take a 2-3 centimeters long strand of hair (diameter of pencil lead) for testing of Ethyl glucuronide (EtG) at baseline, 6-, and 12-month follow-up. EtG in head hair has been presented as the only biomarker that can conclusively discriminate active heavy drinkers from social and non-drinkers (Crunelle et al., 2014). EtG concentration will be a secondary, confirmatory outcome measure. Participants with head hair shorter than 2 centimeters or refusing hair sampling will not be excluded from the study. An additional consent procedure at the end of the baseline procedure since the sampling might be felt as more invasive than questionnaires and brief intervention and might lower participant willingness to participate to the essential parts of the study.

During the pre-testing phase (Aim 1), information and consent procedure will also be used (see Appendices). The participants will be ask if they consent to participate in an audio-recorded brief motivational intervention and a semi-structured qualitative interview. There will be no questionnaires and no follow-up.

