| Other outcomes of interest (questionnaires)                                                                                                                                                                                                      | x                  |                        | x                 | x         | x     | x                               |   |                            |   |
| Randomisation                                                                                                                                                                                                                                    | x                  | x                      |                   |           |       |                                 |   |                            |   |
| Intervention with research clinician:                                                                                                                                                                                                            |                    | x                      |                   |           |       |                                 |   |                            |   |
| Head hair sample (only if hair>2 cm and additional consent)                                                                                                                                                                                      |                    |                        | x                 |           |       |                                 | x |                            | x |
| Consultation of administrative and medical records (only if additional consent)                                                                                                                                                                  |                    |                        |                   |           |       |                                 |   | Not in presence of patient |   |
| Phase 3 – Mechanisms analysis                                                                                                                                                                                                                    |                    |                        |                   |           |       |                                 |   |                            |   |

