#### 11.4.2 Primary Analysis

We will test intervention effects over time by comparing groups on the 2 primary and 6 secondary outcomes. For repeated measures, analyses will be conducted using generalized estimating equations (GEE) with robust standard error estimate (Liang and Zeger, 1986). This approach offers an extension of regression analysis to the case of correlated observations over time; it allows for specification of the assumed correlation structure as well as the appropriate link functions to handle dependent variables with a normal distribution, dichotomous outcomes, count data (Poisson), and over-dispersed count data (negative binomial). Models will all be adjusted for the baseline AUDIT score. For outcomes measured at 12-month only, analyses will be conducted using baseline adjusted regression models.

Analyses will be performed at the completion of data collection.

Analyses will be performed by the study PI ([name]), in collaboration with research collaborator [name], and consulting from study co-Is ([name], [name], [name]) and international collaborators ([name], [name]).

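### Consent for hair ethyl glucuronide is sought after randomisation and the allocated session, so the subset with the only objective drinking measure is formed after allocation: an avoidable risk, not a shown bias

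*Protocol*

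**What the plan says.** Section 9.3.1 gives Day 1 as a lettered sequence: baseline questionnaire (E), randomisation (F), intervention (G), post-session questionnaire (H), counsellor's rating (I), and then, as item J, "Head hair sampling for Ethyl Glucuronide concentration analysis". The first entry under J is "Additional information and consent procedure". In the 9.1 flow chart, the row beginning "Head hair sample (only if hair>2 cm and additional consent" has its first mark in the post-intervention column, not the baseline column. Section 2.7 words the timing differently: "An additional consent procedure will be conducted at the end of the baseline procedures".

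The reason section 2.7 gives for a separate request is that "the sampling might be felt as more invasive than questionnaires and brief intervention", so that asking might reduce willingness to join the essential parts of the study. The other optional consents belong to the initial consent process: "Additional (optional consent) will be asked for the audio-recording of the intervention and consultation of their hospital administrative and medical records".

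Sections 9.3.4 and 9.3.6 make the 6- and 12-month hair appointments conditional on the Day 1 hair consent. Section 5.2 (item g) calls EtG a secondary, confirmatory outcome, measured at baseline, 6 and 12 months and read against concentration cut-offs. On the models, section 11.4.2 says: "Models will all be adjusted for the baseline AUDIT score".

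**The concern.** EtG is in the plan because the drinking outcomes otherwise rest on self-report. The hospital records in 5.2 (item f) cover only start of treatment and emergency-room readmission, so EtG is the only objective measure of drinking.

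Randomisation protects a comparison in a consenting subset if consent is settled before allocation. Here the request follows either 5 to 10 minutes of structured advice or a 20 to 60 minute interview designed to build a relationship and raise motivation. Both willingness to give hair, and which kind of drinker agrees, could differ by arm. Because all later samples depend on this one decision, any imbalance carries into every EtG comparison between arms. The confirmatory result could then contradict a true self-report finding or support a false one.

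**Working it through.** The protocol states no sample size, consent rate or effect for EtG, so there is no figure of its own to reproduce. The 172 per group in 11.2 concerns the primary outcomes and is not affected.

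**Order of events.** Items F and G of 9.3.1 precede J, and the flow chart agrees. If 2.7 is taken literally, it contradicts both. If its baseline procedures loosely mean the whole Day 1 visit, it agrees with them and the request still falls after allocation. The wording needs reconciling either way.

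**Size under assumed rates.** Let p be the proportion of heavy drinkers, equal in both arms (no true effect), and let c_h and c_n be the consent rates among heavy and other drinkers. Among consenters,

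P(heavy | consent) = p·c_h / [p·c_h + (1 − p)·c_n].

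With p = 0.40 (all rates are assumptions):

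- Control, c_h = c_n = 0.50: 0.20/0.50 = 40.0%.
- Brief motivational intervention (BMI), c_h = 0.60, c_n = 0.50: 0.24/0.54 = 44.4%, a spurious 4.4 points against BMI.
- BMI, c_h = 0.65, c_n = 0.50: 0.26/0.56 = 46.4%, 6.4 points against BMI.
- BMI, c_h = 0.40, c_n = 0.50: 0.16/0.46 = 34.8%, 5.2 points in favour of BMI. The direction cannot be predicted.
- BMI, c_h = c_n = 0.60: 0.24/0.60 = 40.0%, no bias. A different overall consent rate alone does no harm.
- Both arms, c_h = 0.60, c_n = 0.50: 44.4% in each, no bias in the comparison of arms.

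Bias therefore needs consent to depend on arm and drinking jointly. Overall consent in the two 4-to-6-point examples is 0.24 + 0.30 = 54% and 0.26 + 0.30 = 56%, against 50% in control. Total consent by arm would barely reveal the problem.

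**Scale against random error.** If half consent and 20% are lost (the upper attrition figure in 11.2), about 172 × 0.5 × 0.8 = 69 per arm remain. The standard error of a difference at 40% is √(2 × 0.4 × 0.6/69) = 8.3 points, so a bias of 4.4 to 6.4 points is roughly half to three quarters of one standard error.

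**What covariates would do.** A simulation on a continuous scale had no true effect and 50% consent. Baseline drinking lowered the log-odds of consent by 0.3 to 0.5 per SD in one arm only. The assumed correlations were 0.5 to 0.7 between baseline and follow-up EtG and 0.5 between AUDIT and baseline EtG. The size of the spurious difference was:

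- unadjusted: 0.08 to 0.16 SD
- adjusted for AUDIT: 0.06 to 0.13 SD
- adjusted for baseline EtG: about 0

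With no dependence of consent on arm, it was about 0 throughout. The near-complete correction arises because selection was simulated through baseline EtG itself. Selection through motivation or rapport would be corrected less well.

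**The case against.** The late request is a reasoned choice. Section 2.7 fears that an invasive request could put patients off the essential parts, which include the intervention, and a signature does not stop someone leaving. This stands as a small cost. However, it argues for a separate request, not for one after randomisation. Loss between E and F could not depend on the allocated session, and 7.4 already replaces those who withdraw before the intervention starts.

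The stakes are limited, and this stands too. EtG is secondary, will not be used to correct self-report, and within-person comparison of the measures does not need a randomised subset.

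A reader might infer more than the protocol supports:

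- **That the EtG comparison is biased, or cannot be separated from who agreed.** No consent rates are given. AUDIT is collected from everyone before randomisation, so consenters and refusers can be compared within arm. The Day 1 strand grew before the session, so baseline EtG is a pre-treatment value that can be adjusted for.
- **That the model ignores baseline EtG.** Section 11.4.2 fixes AUDIT for all models but excludes no further covariate, nor use of the baseline sample as a repeated measure. It counts six secondary outcomes where 5.2 lists seven items, so it is not certain that EtG is covered. Covariates for a secondary outcome may also stand in an analysis plan that is not at hand.
- **That a definite gain in precision is forgone.** The familiar 1 − r² reduction in variance applies to a continuous linear model, whereas 5.2 defines heavy drinking by cut-offs. Only correlation beyond AUDIT would count, and none is given.
- **That the clinician who has just delivered the session asks for hair.** Item J names no one. Section 1.7.4.2 says of the interventionists, "They will conduct both types of interventions", and also gives them recruitment, baseline assessment and the post-session questionnaires, so this is likely but not stated.

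**Conclusion.** The point holds as a design weakness of modest weight. Sections 9.3.1 and 9.1 form the EtG subset after allocation, 2.7 is worded inconsistently with them, and the order was avoidable, since the other optional consents are taken up front. The protocol establishes a risk of arm-dependent selection, not an actual bias. The possible size runs from zero, if consent does not depend on arm, to about 4 to 6 percentage points in either direction under the illustrative rates. Those rates are assumptions, not estimates. The value of adding baseline EtG is mainly that it reduces consent-selection bias; its effect on precision cannot be quantified from the protocol.

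**What to change.** 1. In 9.1 and 9.3.1, move hair information and consent to after the baseline questionnaire (E) and before randomisation (F), and bring 2.7 into line. The strand can still be cut at the end of the visit.
2. In 11.4.2, name baseline EtG alongside AUDIT as covariate for the EtG outcome, among those with a baseline sample.
3. Report hair consent and sample provision at each time point by arm and by baseline AUDIT, since totals by arm can hide the pattern that matters.
4. State, when EtG is interpreted, that attendance at the separate 6- and 12-month hair visits (9.3.5, 9.3.7) is still a selection after allocation, which moving the consent does not remove.

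The cost is one re-ordered step in the electronic case report form, one covariate and one table. A few participants may react to the hair request before the session, but any such loss would precede allocation. The change has to be made before recruitment, because pre-allocation consent cannot be obtained afterwards.

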### **9.3.2 Month 1, by phone**

- Alcohol use (30-day timeline follow-back)
- Readiness to change questionnaire
- Alcohol Abstinence Self-efficacy Scale – Reduced drinking
- Alcohol-related expectancies
- Actual-ideal drinking discrepancy
- Substance use
- Quality of life
- Alcohol treatment
- Trait reactance (Hong) – 14 items
- Alcohol treatment

### **9.3.3 Month 3, by phone**

- Alcohol use (30-day timeline follow-back)
- Alcohol problems and consequences
- Readiness to change questionnaire
- Alcohol Abstinence Self-efficacy Scale – Reduced drinking
- Alcohol-related expectancies
- Actual-ideal drinking discrepancy
- Substance use
- Quality of life
- ER readmission
- Alcohol treatment

### **9.3.4 Month 6, by phone**

- Alcohol use (30-day timeline follow-back)
- Alcohol problems and consequences
- Readiness to change questionnaire
- Alcohol Abstinence Self-efficacy Scale – Reduced drinking
- Alcohol-related expectancies
- Actual-ideal drinking discrepancy
- Substance use
- Quality of life
- ER readmission
- Alcohol treatment
- Set appointment for head hair sampling (if baseline consent)

**9.3.5 Month 6, hair sampling (at Alcohol Treatment Centre)**

- Sampling of 2-3 centimetres long strand of hair (diameter of pencil lead)

**9.3.6 Month 12, by phone**

- Alcohol use (30-day timeline follow-back)
- Alcohol problems and consequences
- Alcohol Use Disorder Identification Test
- Substance use
- Quality of life
- ER readmission
- Alcohol treatment
- Set appointment for head hair sampling (if baseline consent)

**9.3.7 Month 12, hair sampling (at Alcohol Treatment Centre)**

- Sampling of 2-3 centimetres long strand of hair (diameter of pencil lead)

**9.3.8 Month 12, not in presence of the participant**

If the participant consented to have their administrative and medical records consulted by the study team, a research collaborator specifically trained will access CHUV's administrative and medical records to collect participants' information regarding

- ER readmission
- Alcohol treatment

over the 12-month follow-up period.

## 10. SAFETY

This study falls into the “Other Clinical Trial”, in the Category of risk A.

The current clinical trial is neither a trial of therapeutic products or transplant products, nor a trial of transplantation. The health-related intervention investigated (i.e., a brief alcohol-related motivational interviewing) entails only minimal and temporary risks and burdens on participants’ health (i.e., well-being). The health-related intervention investigated (i.e., a brief alcohol-related motivational interviewing) is recognized as standard in guidelines prepared in accordance with internationally accepted quality criteria. For example, a recent report by the European Monitoring Centre for Drugs and Drug Addiction (2016) concluded that the potential benefits of brief interventions for alcohol and drug users needed to be further studied, yet the feasibility of such interventions, the absence of reported adverse effects and the potential cost-effectiveness suggested that brief interventions could be considered as part of the training for emergency department healthcare professionals.

The risks of serious adverse consequences as a result of study participation are relatively low. It is possible that some participants will find the interviewing tiresome. They might also have concerns about confidentiality of sensitive information addressed during the intervention. The sensitive nature of some of the questions (e.g., alcohol-related) may cause participants discomfort. Acknowledging these risks, care and attention will be given to implement the interviews using nonjudgmental language and delivery. Second, participants will be informed of the sensitive and personal nature of the interview during the consent process and will be informed that they may refuse to participate or skip any questions they do not wish to answer. Participants will also be encouraged to contact one of the investigators/collaborators in case they may have any questions or concerns regarding the study or encounter any stress resulting from study participation. In case participants would find participating in the study too tiresome or intrusive, they will be free to easily withdraw from the study by asking the research clinician to stop the interview (baseline and booster interventions), or deliberately not answering or stopping the phone call (follow-up questionnaires).

